### Complementary examinations

An electromyography is made of the paraspinal muscles in order to determine the ratios of muscle activity on the convex and concave side of the main scoliotic curve.

For the electromyographic measurements, 12 EMG electrodes are placed symmetrically along the superficial erector spinae muscles at three levels, 30 mm from the midline, and parallel to the spinous processes (figure 3). The electrode levels correspond to both end vertebrae of the curve (most tilted ones), and the apex vertebra (Figure 3).

**Figure 3 F3:**
[figure not shown]
**The placement of 6 pairs of bipolar surface EMG electrodes on the paraspinal muscles of the scoliotic spine**. L indicates the lower end-vertebra, U the upper end-vertebra, and A the apex vertebra

The ECG is measured from two electrodes at the sternum and ictus cordis. The electrodes are connected to a multichannel recording device (Porti system, TMS International, Enschede, The Netherlands). Raw EMG signals are amplified, AD-converted, and stored at a sampling rate of 800 Hz in a computer for analysis. The EMG signals are full-wave rectified and low-pass filtered. Reliability data for these specific EMG measurements are available from Cheung et al [3].

The EMG signals are recorded in 5 postures: 1) with the patient in a relaxed upright standing posture with the arms along the body and feet together, 2) with the patient bending to the right, 3) with the patient bending to the left, 4) with the patient bending forward, 5) with the patient sitting in a relaxed position in a chair, with the arms along the body and the back against the chair.

The paraspinal activity (EMG) ratio is defined as the EMG activity of the erector spinae muscles between a convex electrode pair divided by the EMG activity between a contralateral concave electrode pair. The EMG ratios of all 3 levels are considered.

### Outcome measurements

Longitudinal data will be acquired for:

• Scoliotic curve progression (in degrees Cobb angle)

• Height, and growth velocity of height

• Sitting height, and growth velocity of sitting height

• Leg length, and growth velocity of leg length

• Foot length, shoe size, and growth velocity of foot length and shoe size

• Weight, and growth velocity of weight

• Spinal length, and growth velocity of spinal length

• Tanner stage of secondary sexual characteristics

• Riser sign and status of the triradiate cartilage

• Skeletal age in hand, wrist, and elbow

• EMG ratios of the paraspinal muscles

Finally, an algorithm will be developed for predicting peak growth velocity of height and curve progression in individual patients with adolescent idiopathic scoliosis (see Figure 4). 

**Figure 4 F4:**
[figure not shown]
**Summary of the study protocol**.

### Time frame

The first patients will be included in January 2010. An exact date for ending of this study is not provided as it will be incorporated in the usual care of AIS patients, and it is aimed to proceed for the coming years. The first evaluation of the results is expected to take place 2.5 years after the start of the study, in July 2012. In that time, 25 patients are expected to have fulfilled a two-year follow up time.

### Sample size and statistical analysis

The maximum sample size of this study is not determined on beforehand, as the study is aimed to proceed for the coming years.

We aim to perform a first preliminary analysis of the longitudinal data when patients have a follow up of at least 2 years. As the expected number of new patients is 60 each year, it will take 2.5 years for 30 patients to reach a follow up of at least 2 years. Taking a loss to follow up into account due to surgical treatment, we expect to be able to analyse the complete data of at least 25 patients. The statistical power will increase with a longer follow up and more patients. The number of 25 patients was checked whether it was large enough to obtain a good prediction model according to the criteria of Knofczynski and Mundfrom [33]. With a significant large influence of 4-5 predictor variables (as is expected in this study) and a squared multiple correlation coefficient between 0.5 and 0.7 between 25 and 65 patients should be included. Therefore the first preliminary analysis will be performed using data of 25 patients.

Individual data charts are made, and results of each parameter are plotted against the growth velocity of total body height and the curve progression.

All statistical calculations are made using SPSS (SPSS Inc, Chicago USA). Pearson correlation coefficients are computed for each individual possible related parameter against the peak growth velocity and the curve progression (Figure 5). A correlation above 0.70 is believed to be clinically relevant. To be able to interpret this value in a reliable way, we will report the confidence intervals as well.

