The peak growth spurt is known to take place between 10 and 14 years in 95% of the girls, and between 12 and 16 years in 95% of the boys[8,9]. This range holds for a large population, but is too wide to make accurate predictions in the individual patient. However, several other maturity indicators are related to the pubertal growth spurt. Maturity is multidimensional and has various components, including chronological age, skeletal age in different areas, the Risser sign, status of the triradiate cartilage, Tanner stage of sexual maturation, age at thelarche and menarche, and several length dimensions like sitting height, subischial leg length, and foot length or shoe size. These indicators of maturity are all signs that reflect growth or remaining growth of the patient and can be useful in predicting timing of the pubertal growth spurt or peak growth velocity of total body height in the individual patient.

Researchers have tried to find different ways to predict curve progression in AIS as well, besides relating progression to the peak growth velocity of height. A promising method was shown by Cheung et al[3,10], who found a relationship between curve progression and altered electromyography ratios of the convex and concave sides of the curve. Enhanced EMG ratios were observed at three levels of the scoliotic curve (lower end vertebra, apex, and upper end vertebra) at the start of progressive periods. At the start of a non-progressive period, such an enhanced EMG ratio was only observed at the level of the apex vertebra[3].

Only few studies have investigated maturity indicators in patients with idiopathic scoliosis[11-14]. Moreover, studies have compared only some of these indicators, and only either in relationship to the peak growth velocity of total body height, or to curve progression, not to both in one study. Results of different studies are contradictory and inconsistent, so therefore a good algorithm for determining treatment options in AIS is still lacking.

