### Body length dimensions

It is known that different body length dimensions each have their own typical growth pattern influenced by age- and gender-related factors. Research has been done by Welon and Bielicki[15], Cameron et al[16], Dimeglio[17], and Rao et al[18] to the sequences of peak growth velocities of different length measurements of children from 1-18 years. They all confirm the distal-to-proximal growth maturity gradient as described by Tanner[19]. Body parts that are more distal will have their pubertal growth spurt earlier in adolescence. Furthermore, it is known that the sequence of growth spurts of different length measurements is similar in individual children, regardless of being an "early" or "late" maturer[4,20]. Therefore different body length growth velocities can be useful in predicting peak growth velocity of total height.

In order to calculate growth velocities, access is needed to longitudinal growth data of the patient. It is useful when a patient already has some measurements known at the first visit to the outpatient clinic. Usually that happens very rarely. However, as foot length is said to be the body dimension with the earliest pubertal growth spurt[17,18,21-23], patients were asked if they could recall the course of their shoe size. In a pilot study, it was shown that patients and their parents can recall to a high extend when they bought new shoes and what their shoe size was for approximately the last 2 years. This could therefore be a better measurement than foot length. However, this study should investigate the possibility of a recall bias in a larger dataset, as well as the reliability of the provided information.

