### Identification and recruitment of study participants

Patients between 8 and 17 years old, visiting the outpatient clinic of the UMCG with adolescent idiopathic scoliosis will be participating in this study. The Cobb angle should be >10 degrees, measured by an experienced observer on an AP X-ray of the total spine.

Patients should not have had previous spinal surgery; there should be no evidence of neuromuscular disease or skeletal dysplasia, and no evident abnormalities of maturation or height. Furthermore, patients with mental incapacitation are excluded since this can influence the reliability of the measurements in the way that these patients most often can not stand still during the height measurements and EMG measurements. Patients are excluded as well when they are participating in a different study simultaneously.

The assessment to include or exclude a patient will be determined by the orthopaedic surgeon. All patients who meet the inclusion criteria will be asked to participate in this study and give their informed consent.

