### Study protocol

The study protocol will be incorporated in the usual care of patients visiting the outpatient clinic for follow up of adolescent idiopathic scoliosis. Follow up will take place every six months. Patients will be followed until 18 years of age or until growth of the spine has stopped and skeletal maturity has been reached. Furthermore, patients will be lost to follow up when they receive surgical treatment.

A description of the (follow up) consult is presented below.

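### The 25 patients offered as sufficient for the first analysis are patients with two years of follow-up, not patients with an observed growth peak, so the plan's own minimum is not met for the peak-velocity models

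*Protocol article*

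**What the plan says.** Under Sample size and statistical analysis, the protocol article gives an intake at which "the expected number of new patients is 60 each year" and concludes that "it will take 2.5 years for 30 patients to reach a follow up of at least 2 years". Surgery is the only reason given for losing any of these 30, and the result is put as follows: "we expect to be able to analyse the complete data of at least 25 patients". It then checks 25 against a published criterion. With 4-5 influential predictors and a squared multiple correlation of 0.5 to 0.7, that criterion asks for 25 to 65 patients. The analysis at 25 is called preliminary, and no maximum sample size is set.

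The same section plans multiple linear regressions for the timing and magnitude of peak height velocity and for curve progression, and correlations of each parameter with both outcomes.

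Four other statements bear on how many peaks can be seen:
- Identification and recruitment of study participants: "Patients between 8 and 17 years old", with no restriction to patients before their peak.
- Background: "The peak growth spurt is known to take place between 10 and 14 years in 95% of the girls"; the corresponding range for boys is 12 to 16.
- Body length dimensions, on patients who bring earlier measurements to the first visit: "Usually that happens very rarely".
- Study protocol, where visits are six-monthly: "Patients will be followed until 18 years of age or until growth of the spine has stopped". The second of these end points also requires skeletal maturity. Surgery ends follow-up too.

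**The concern.** The adequacy check counts completed follow-up. That is a reasonable unit for curve progression, which can be measured in anyone followed for two years. It is the wrong unit for peak velocity. A patient already past the peak at entry, or not yet there after two years, has no observed value of the outcome. The plan sets 25 against its criterion without distinguishing the two outcomes.

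At stake is the precision of the first peak-growth equations and correlations, which are meant to feed an algorithm for individual patients. The article regards a correlation above 0.70 as clinically relevant and will report confidence intervals. With few observed peaks, those intervals would be too wide to place a correlation relative to 0.70.

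A smaller issue concerns the 25 itself. Surgery is the only loss named between 30 and 25, although the article has two further reasons for leaving follow-up.

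**Working it through.** **The plan's own figures.** 60 per year × (2.5 − 2.0) years = 30, which reproduces exactly. Going from 30 to 25 implies a loss of 5/30 = 16.7%. No rate is stated, so 25 is consistent with the text but not derived from it. The 25 to 65 range comes from a cited source and is taken as stated.

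**Age at peak.** Treat the 95% ranges in the Background as normal: mean 12 years for girls and 14 for boys, SD = 2/1.96 = 1.02 years.

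**Assumed entry ages.** The article gives only the limits 8 and 17, so the distribution and the sex mix (50%, 80% or 100% girls) were varied. Among patients entering by age 16, who can complete two years before 18, two quantities were simulated, with w = age at peak − age at entry:
- peak within two years: 0 ≤ w ≤ 2;
- peak with at least one full six-month interval on each side: 0.5 ≤ w ≤ 1.5.

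| Entry age (assumed) | Peak within 2 years | Of 25 | Bracketed, of 25 |
|---|---|---|---|
| Uniform 8-17 | 25% | 6.2 | 3.1 |
| Uniform 10-16 | 27-30% | 6.7-7.5 | 3.4-3.8 |
| Uniform 10-14 | 40% | 10.0 | 5.2 |
| Normal, mean 12, SD 1.5 | 37% | 9.1-9.2 | 4.7 |
| Normal, mean 13, SD 1.5 | 25-34% | 6.2-8.4 | 3.1-4.3 |
| Normal, mean 14, SD 1.5 | 13-27% | 3.4-6.7 | 1.6-3.4 |

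Ranges within a row reflect the sex mix. The first row can be checked by hand: uniform entry over the eight years from 8 to 16 with a two-year window gives 2/8 = 25%.

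**Best case at a common entry point.** If every patient entered exactly one year before the mean peak age for their sex, the proportion peaking within two years is 2Φ(1/1.02) − 1 = 0.67, and 25 × 0.67 ≈ 17. The bracketed proportion is 2Φ(0.5/1.02) − 1 = 0.38, or about 9 of 25. The first entrants have between 2.0 and 2.5 years of follow-up in July 2012. Giving all of them 2.5 years, with the peak centred in that window, yields 2Φ(1.25/1.02) − 1 = 0.78, or about 19.

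**Completed patients needed for 25 peaks within two years.** 25/0.40 ≈ 63 in the most favourable row, 25/0.25 = 100 under uniform entry at 8-17, and 25/0.134 ≈ 186 in the least favourable case.

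**Precision.** The 95% interval for an observed r = 0.70 is tanh(atanh 0.70 ± 1.96/√(n − 3)). Residual degrees of freedom with five predictors and an intercept are n − 6.

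| n | 95% CI for r = 0.70 | Residual df |
|---|---|---|
| 25 | 0.42 to 0.86 | 19 |
| 17 | 0.33 to 0.88 | 11 |
| 10 | 0.13 to 0.92 | 4 |
| 6 | −0.26 to 0.96 | 0 |

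**Exit at 18.** Anyone entering after 16.0 cannot complete two years. Under the assumed ages this is 0 to 11% of entrants; 30 × 0.11 ≈ 3, so 0 to 3 of the 30. The maturity exit cannot be quantified from the article.

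**The case against.** The strongest reply is that this is openly a first preliminary look at an open-ended cohort. The article says that power grows with longer follow-up and more patients. Follow-up normally continues to 18 or maturity, so patients who have not peaked by July 2012 will mostly supply their peak later. Only those past the peak at entry are lost for good to the peak models. All of this stands, and it limits the point to the first analysis. A reader might infer that the study's main question as a whole rests on a handful of patients; the article does not support that.

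Four other stronger readings also fail:
- **That the exit rules take patients out of the 25.** The 25 are already patients with complete two-year data, and surgery has been deducted. Exit at 18 or maturity reduces the 30, which threatens the claim of at least 25. For the peak models this largely overlaps with the main point, because late entrants are mostly past their peak.
- **That the plan will take the highest velocity at the edge of follow-up as the peak.** The article never says so. How unobserved peaks are handled may be settled in an analysis plan that is not shown.
- **That the whole first analysis is undersized.** The 25 serve both outcomes, and two-year curve progression can be measured in all of them.
- **That no regression would be possible.** At 17 patients one could be fitted; at 6, with five predictors, no residual degrees of freedom remain.

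The counts also depend on assumed entry ages. That affects the size of the shortfall, but every assumption tried leaves the count below 25. What remains is not an omission to be excused by the article format: the article states a number, derives it and declares it sufficient for regressions that include peak velocity.

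**Conclusion.** The point holds for the peak-velocity models at the first preliminary analysis. About 3 to 10 of the 25 patients would be expected to peak within two years, about 2 to 5 with an interval on each side, and about 17 in the best case of perfectly timed entry, against a stated minimum of 25. These figures rest on normally distributed peak ages derived from the article's 95% ranges and on assumed entry ages and sex mix. An observed peak in all 25 is not strictly impossible, but its probability was about 1 in 10 billion or less in every tabulated scenario.

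The uncounted exits are a secondary matter: 0 to 3 of 30 for age under the same assumptions, and an unknown number for maturity. They bear mainly on whether 25 is reached for curve progression.

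**What to change.** 1. State the expected evaluable number separately for curve progression and for peak height velocity.
2. Run the peak-velocity correlations and regressions only once the number of patients with an observed peak, bracketed by lower velocities before and after, reaches the stated minimum of 25.
3. State that the highest velocity in the first or last interval of follow-up is not treated as the peak. A censored-data model for timing is an option that would let patients without an observed peak contribute. It would not address magnitude, and it is not required.
4. In the step from 30 to 25, allow for exit at 18 and at skeletal maturity as well as surgery, giving the assumed rates.

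The cost is wording and a later date for the peak-growth results, which would follow the curve-progression results. Because recruitment and follow-up continue, no change to the design is needed.

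### The plan's own check asks for 25 to 65 patients, so its conclusion that 25 are enough for a prediction model holds only at the most favourable end of that range

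*Protocol article*

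**What the plan says.** All of the sample-size reasoning is in the article's section on sample size and statistical analysis.

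- **Accrual:** "As the expected number of new patients is 60 each year, it will take 2.5 years for 30 patients to reach a follow up"; the duration meant is two years or more. After losses to surgery, "we expect to be able to analyse the complete data of at least 25 patients".
- **Criterion:** the 25 is tested against a published rule for good prediction models. The premise is "With a significant large influence of 4-5 predictor variables (as is expected in this study"), and the result is that with "a squared multiple correlation coefficient between 0.5 and 0.7 between 25 and 65 patients should be included".
- **Conclusion:** "Therefore the first preliminary analysis will be performed using data of 25 patients".
- **Analysis:** each possibly related parameter is correlated with peak growth velocity and with curve progression. Multiple linear regression then gives equations for three outcomes: timing of peak growth velocity, its magnitude, and curve progression.
- **Later growth of the sample:** no maximum is set, and "The statistical power will increase with a longer follow up and more patients".
- **End product:** under Outcome measurements, "an algorithm will be developed for predicting peak growth velocity of height and curve progression in individual patients".

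**The concern.** A requirement of 25 to 65 does not lead to 25 unless there is a reason to expect the conditions at the lower end. The article gives none. It assumes an R² anywhere between 0.5 and 0.7 and then takes the number that suits only the best case.

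The rule is also entered with 4-5 predictors, while the article measures many more indicators and does not say which 4-5 are meant. If the data on 25 patients decide which ones enter, the rule no longer describes the analysis.

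At stake is how far the first equations can be trusted. Their R² would look better in the 25 patients than it would in the next patient, and 25 is the only sample size that the article justifies for any model.

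**Working it through.** **1. Accrual figure.** Inputs from the sample-size section: 60 patients per year, 2 years of follow-up, analysis at 2.5 years. 60 × (2.5 − 2.0) = 30, which reproduces the article. 25/30 implies a loss of 16.7%.

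**2. The 25-65 range.** It comes from a cited source that is not shown, so it cannot be reproduced exactly. Browne's formula for the squared correlation between predicted and observed values in new patients shows which end goes with which R²:

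ρc² = [(n−k−3)ρ⁴ + ρ²] / [(n−2k−2)ρ² + k]

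For example, with n=25, k=5, ρ²=0.7: (17×0.49 + 0.7)/(13×0.7 + 5) = 9.03/14.1 = 0.640, and √(0.640/0.7) = 0.96. The ratio of new-patient to true multiple correlation for k = 5 and k = 4 is:

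| n | ρ² = 0.7 | ρ² = 0.5 |
|---|---|---|
| 25 | 0.96-0.97 | 0.91-0.93 |
| 65 | 0.99 | 0.97-0.98 |

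So 25 patients at R² = 0.5 do clearly worse than 25 at R² = 0.7. Matching the latter's accuracy at R² = 0.5 takes about 49-50 patients by this approximation; the article's own range runs to 65.

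**3. Size of the optimism with 5 fixed predictors and true R² = 0.5.** No variable selection is involved here.

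- Apparent R² ≈ 1 − (1−ρ²)(n−k−1)/(n−1)
  - n=25: 1 − 0.5×19/24 = 0.60
  - n=65: 1 − 0.5×59/64 = 0.54
- New-patient R² = 1 − (1−ρ²)(1+1/n)(n−2)/(n−k−2)
  - n=25: 1 − 0.5×1.04×23/18 = 0.34
  - n=65: 1 − 0.5×(66/65)×63/58 = 0.45

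The gap falls from 0.27 to 0.09. The last formula measures squared prediction error, a stricter yardstick than the correlation in step 2.

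**4. Number of candidates.** From the Outcome measurements list, read with the examination sections:

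- 7 size measures and their 7 velocities = 14
- breast and pubic hair stages = 2
- Risser sign and triradiate cartilage = 2
- hand/wrist and elbow skeletal age = 2

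That makes 20. Adding EMG ratios at 3 levels gives 23. Since "The EMG signals are recorded in 5 postures", counting every level-by-posture ratio adds 15 instead of 3 and gives 35. For the growth outcomes, EMG is not put forward as a predictor, height velocity underlies the outcome, and leg length is height minus sitting height. That leaves 20 − 2 = about 18. History items and arm span are not counted.

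**5. Pure noise, best 4 or 5 forced in by forward selection** (simulated, with independent and with correlated candidates):

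| n | Candidates | Mean R², best 4 | Mean R², best 5 |
|---|---|---|---|
| 25 | 18 | 0.45-0.46 | 0.50-0.51 |
| 25 | 23 | 0.49-0.50 | 0.55-0.56 |
| 25 | 35 | 0.56-0.57 | 0.63-0.65 |
| 65 | 23 | 0.20 | 0.22-0.23 |
| 65 | 35 | 0.24 | 0.27-0.28 |

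Other rules give less. At n=25 with 35 candidates, entry at p<0.05 gives a mean of 0.14-0.41, and taking the five largest Pearson correlations gives 0.22-0.50; the higher values belong to independent candidates.

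**6. Time to 65 analysed.** 65/(25/30) = 78 enrolled; 78/60 = 1.3 years of accrual; plus 2 years of follow-up = 3.3 years. Against 2.5 years this is 0.8 years, about 10 months later.

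**The case against.** The strongest case on the other side has four parts.

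- **The analysis is called preliminary.** Accrual continues, power is expected to grow, and the algorithm is placed at the end of the programme. No sentence says that the 25-patient equations feed it. This stands and lowers the severity. It does not repair the inference, because the 25 was tested explicitly as enough for a good prediction model and no later size is fixed.
- **A reader might infer that noise alone would reproduce the assumed R².** The documents do not support that. They state no selection rule, and step 5 shows that the result depends on the rule. Measured against 0.7, even the best 5 of 35 noise candidates get there in only 22-29% of runs. The defensible word is could.
- **A reader might also infer that candidates outnumber patients.** That needs all 15 EMG ratios. The article lists EMG ratios as one item and says that the three levels are considered; on that reading the count is 18-23, below 25. It is still about four to five times the 4-5 assumed.
- **Lack of a validation step or of named predictors is silence.** In a condensed article with no analysis plan shown, this is not a finding. These items appear under the fix only as safeguards.

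The link between 25 and R² = 0.7 is also an inference. The range may partly reflect 4 versus 5 predictors.

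**Conclusion.** The conclusion that 25 patients suffice does not follow from a requirement of 25 to 65. It holds only at the favourable end of the article's assumptions, presumably R² near 0.7 with the fewest predictors; step 2 agrees with that reading, but the cited source is not shown.

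This holds whatever selection rule is used. At a true R² of 0.5 with 5 fixed predictors, about 0.60 would be reported and about 0.34 achieved in new patients. If the best 4-5 are instead chosen from 18 to 35 candidates on the same patients, noise could by itself give about 0.45-0.65. That range assumes forced forward selection, and p<0.05 entry gives less. The formulas assume multivariate normal data.

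Severity is moderate: the stated justification is wrong as written, but the analysis is preliminary and the study goes on enrolling.

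**What to change.** 1. Restate the sample-size sentence: 25 patients satisfy the cited criterion only at the favourable end of the assumed range, and up to 65 are needed at the other end.
2. Keep the 2012 analysis to the individual charts and the correlations with confidence intervals that are already planned.
3. Fit the prediction equations at about 65 analysed patients (about 78 enrolled, about 3.3 years after start). The planned accrual reaches this without extra recruitment.
4. If equations are fitted at 25 all the same, use 4-5 predictors per outcome fixed in advance, report a bootstrap optimism-corrected R², and label the equations exploratory and not for use in the treatment algorithm.

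Cost: some rewording and, if option 4 is taken, a little more analysis. Otherwise the equations come about 10 months later. Either way, the reported R² will look less favourable.
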